Electroencephalogram (EEG) is an important method for assessing brain function and widely used in clinical practice. It tracks and records the tiny electrical signals produced by cortical neuronal activity in real time by placing electrodes on the scalp. Brainwaves in different frequency bands reflect synchronized neuronal activities across distinct brain regions (19). Since EEG has a temporal resolution in milliseconds, it can capture changes in neuronal electrical activity more rapidly than MRI and is highly sensitive to abnormalities in brain metabolism and neural function (20). Due to its simplicity and non-invasive nature, EEG has been applied to evaluate the therapeutic effect after intervention for brain diseases. As evidenced by EEG, in stroke patients with better clinical outcomes, the healthy hemisphere tended to compensate for the affected side, and kinematic and EEG metrics were reported to be relevant for evaluating early post-stroke motor recovery (21). Additionally, event-related desynchronization (ERD) during action observation, reflecting reduced coordination of neural activity, was validated as an early predictor of motor recovery in subcortical stroke (22). These metrics provide important prognostic information that can be used to optimize treatment strategies. Herein, we design a randomized, assessor-and-statistician-blinded, parallel-controlled clinical trial, for assessing the efficacy and safety of acupuncture therapy, featuring acupoint combination for “simultaneous treatment of phlegm and blood stasis,” in treating limb dysfunction in ischemic stroke patients with hemiplegia. We will employ functional scales to evaluate patients’ clinical outcomes and use EEG to capture neurophysiological changes after acupuncture, including neural excitability and brain functional connectivity. Further, EEG metrics will be linked with clinical outcomes, demonstrating its multiple values in efficacy assessment, mechanism interpretation, and prognosis prediction.

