##### EEG data processing

2.12.2.7

EEG signals collected from electrodes placed at different head regions are filtered to remove interference signals with frequencies below 0.5 Hz and above 30 Hz. Independent component analysis (ICA) is applied to eliminate non-cerebral interferences from the EEG data, such as electrooculography (EOG) artifacts and electromyography (EMG) signals. After amplified, the processed signals are input into a computer’s analog-to-digital converter (ADC), where the waveform signals are transformed into digital information and stored in the computer’s memory. Fast Fourier Transform (FFT) will analyze voltage variables at different time phases to process the power spectra across various frequency bands. The full-band spectral power plot is displayed with a frequency resolution of 1 Hz per step, and power plots are generated for the four frequency bands: delta (1–4 Hz), theta (4–8 Hz), alpha (8–13 Hz), and beta (13–30 Hz). The grayscale images will be converted into color bands, their grayscale levels will be numerically quantified, and a grayscale scale will be generated for analysis using BESA (Brain Electrical Source Analysis, BESA) software.

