##### Coherence analysis

2.12.2.8

Coherence is an index used in EEG analysis to measure signal synchrony between two brain regions, reflecting the degree of functional connectivity between them. The coherence C*_xy_* (*f*) between two EEG signals *x* and *y* from different electrodes at frequency *f* is calculated using the following formula:

$$C_{\mathrm{xy}}(f)=\frac{|P_{\mathrm{xy}}(f)|2}{P_{\mathrm{xx}}(f).P_{\mathrm{yy}}(f)}$$

*P_xx_* (*f*) and *P_yy_* (*f*) represent the power spectral densities of signals *x* and *y*, respectively, while *P_xy_* (*f*) is the cross-spectral density between *x* and *y*, all of which are estimated using the Welch method. Coherence ranges from 0 to 1, with higher values indicating greater similarity in phase and amplitude between EEG signals, among which, a value of 1 indicates complete synchronization, while 0 indicates complete desynchronization. This study will calculate coherence in the alpha and beta bands, designating the M1 region (primary motor cortex) on the ipsilesional or contralesional side of the lesion as the seed region, and will calculate coherence values between the seed region and all other regions. In the 32-electrode layout of the international 10–20 system, the M1 seed region is defined as C3 (for the left hemisphere M1) or C4 (for the right hemisphere M1). When the infarct lesion is located in the right hemisphere, the data will be flipped along the midline to standardize the analysis hemisphere. For normally distributed data, two independent-samples t-test will be conducted, while for non-normally distributed data, non-parametric Wilcoxon test will be applied to compare Coherence differences between the two groups. Additionally, Cohen’s *d* will be calculated to quantify the effect size, and the Bonferroni correction will be employed to control the false positive rate associated with multiple comparisons.

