### Statistical analysis

2.16

All data will be analyzed using SPSS 27.0 statistical software. In accordance with the intention-to-treat (ITT) principle, patients who have received at least one treatment session will be included in the analysis. Basic information, baseline data, and efficacy evaluation will be analyzed using both the full analysis set (FAS) and per-protocol set (PPS). In case of inconsistent results between the two datasets, further analysis and evaluation will be conducted. Missing data will be imputed using multiple imputation method. For continuous outcomes, post-treatment data are presented as mean±SD if normally distributed with equal variances; otherwise, they are presented as median (IQR). ANCOVA will be used to adjust for baseline values and confounders (e.g., age, gender, revascularization therapy status), with adjusted mean differences and 95% CIs reported. For categorical data, frequencies and percentages will be presented, and potential confounders will be screened via univariate analysis before constructing stepwise logistic regression models to adjust for confounders and report odds ratios with 95% CIs, followed by validation of the model’s goodness of fit. Further, patients will be grouped based on infarction location to analyze EEG indicators in each subgroup. Receiver operating characteristic (ROC) curve analysis will be conducted to evaluate the predictive value of EEG as an efficacy indicator for acupuncture response, with the area under the curve (AUC) and 95% CI reported. For correlation analysis, Pearson correlation will be applied to normally distributed continuous data, while Spearman correlation will be used for ordinal data. All data analysis will be conducted using two-tailed tests with a significant level of 5%.

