## Discussion

3

Since ischemic stroke poses a severe threat to health, thrombolysis and thrombectomy after acute stroke can effectively reduce stroke-related mortality and disability rates (30). However, the strict time window for these treatments limits stroke patients’ therapeutic benefits (31). Most patients experience varying degrees of neurological deficits after acute stroke, with approximately 50–80% developing limb motor dysfunction related to ischemic lesion during recovery period, which indicates a significant demand for post-stroke functional rehabilitation (32). The Stroke Roundtable Consortium defines the first 24 h post-stroke as the hyperacute phase, the first 7 days as the acute phase, the first 3 months as the early sub-acute phase, 4–6 months as the late sub-acute phase, and beyond 6 months as the chronic phase (33). In the early post-stroke period, a series of neuronal plasticity-enhanced mechanisms trigger dendritic growth, axon sprouting, and the formation of new synapses (34). The “proportional recovery rule” suggests that patients can recover approximately 70% of lost function within 3–6 months post stroke (35), though this proportion varies with individual differences, lesion location and severity, as well as the effectiveness of rehabilitation measures. Therefore, seizing the critical time window for post-stroke rehabilitation and implementing effective rehabilitation measures are crucial for restoring impaired neural functions, improving disease prognosis, and enhancing patients’ quality of life.

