
Outcome measures include the simplified Fugl-Meyer Assessment for motor function, the Berg Balance Scale, the Fugl-Meyer Assessment for sensory function, the Modified Ashworth Scale, the Modified Barthel Index, and TCM syndrome scoring scale, which are used to comprehensively evaluate the efficacy of the “simultaneous treatment of phlegm and blood stasis” acupuncture therapy based on syndrome differentiation on improving limb mobility, balance, sensation, muscle tone, activities of daily living, and TCM-related symptoms/signs in ischemic stroke patients with hemiplegia. Resting-state EEG is highly sensitive to cerebral metabolic and neurological functional abnormalities, serving as an important method for assessing post-stroke brain function (38). Commonly used frequency bands in EEG include alpha, beta, theta, and delta waves. Alpha wave activity during rest reflects the level of consciousness and visual attention (39). With a frequency range of 8–13 Hz, alpha waves are brain rhythms involved in various functions, ranging from sensorimotor processing to memory formation (40). Research indicates a linear relationship between reduced synchrony of alpha wave oscillations among brain regions and cognitive/motor function impairments in stroke patients (41). Beta waves, oscillating at 13–30 Hz, are crucial rhythms in cortical activity, closely related to motor control and sensorimotor integration (42), with their generation involving the synergistic action of pyramidal and inhibitory neurons (43). Research has found that beta wave coherence can serve as a marker for cortical functional plasticity after stroke (42). Delta waves are low-frequency waves with frequencies ranging from 1–4 Hz, and can be detected during slow-wave sleep and execution of cognitive tasks (44). Theta waves, with frequencies in the 4–8 Hz range, have been extensively studied in emotional and cognitive domains. Recent research has found that perturbation during seated movements can evoke differential theta-band responses in the anterior cingulate cortex and supplementary motor areas (45). In this study, we will employ EEG to record and analyze the frequency, amplitude, and spectral power of delta, theta, alpha, beta waves. We will designate the M1 region as the seed region and calculate the coherence of alpha and beta waves between the seed region and other regions. By observing changes in neuronal oscillation frequencies, electrical activity intensity, and functional connectivity across different brain regions before and after treatment, we aim to explore the neurophysiological mechanisms, by which acupuncture improve limb function in stroke patients, and screen EEG-based biomarkers with predictive value.

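### The planned ROC analysis can show that EEG predicts recovery, but with no comparison of the marker between acupuncture and sham it cannot show that EEG predicts response to acupuncture

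*Protocol article*

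**What the plan says.** Section 2.16 (Statistical analysis) gives one analysis for the predictive use of EEG: "Receiver operating characteristic (ROC) curve analysis will be conducted to evaluate the predictive value of EEG as an efficacy indicator for acupuncture response". The result is to be an AUC and its 95% CI. The section does not name the arm or arms that enter, the definition of response, or whether the EEG value is the baseline one or the change. It plans no marker-by-arm comparison, and none appears elsewhere in the article.

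The Discussion says the trial will "screen EEG-based biomarkers with predictive value"; the abstract states the same aim. The Introduction expects to link EEG to clinical outcome, "demonstrating its multiple values in efficacy assessment, mechanism interpretation, and prognosis prediction".

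The data for a between-arm comparison will exist: section 2.1 and Table 1 schedule EEG and the scales in both arms, before treatment and on Day 15. Section 2.16 already plans an ANCOVA with baseline adjustment.

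Three further statements bear on interpretation. Section 2.4 admits patients 1 week to 3 months after onset. Section 2.10.1 gives every patient rehabilitation five times a week for the two weeks. The Discussion, citing the proportional recovery rule, says that "patients can recover approximately 70% of lost function within 3–6 months post stroke".

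**The concern.** An ROC curve asks whether a marker separates patients who improved from those who did not. Predicting response to acupuncture is a different question: whether the benefit of acupuncture over sham differs by marker level. Only a contrast between arms can answer it, because no patient is seen under both treatments.

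In this population some improvement is expected in both arms, so a patient who improves under acupuncture has not necessarily improved because of it. The Introduction itself cites EEG measures as relevant to, or early predictors of, motor recovery in general. That makes a prognostic marker quite likely to be found. The risk is that such a marker is published as identifying who benefits from acupuncture when it would do equally well under sham.

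**Working it through.** **Inputs from the article.** Section 2.7: δ = 6.59, σ = 7.81, two-sided α = 0.05 (two-tailed per section 2.16), power 0.90. The stated size reproduces: 2 × (1.960 + 1.282)² × 7.81² / 6.59² = 29.5, so 30 per arm; 30 × 1.15 = 34.5, so 35 per arm and 70 in all. No figure is given for the ROC analysis.

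**Assumptions, not in the article.** The 7.81 is used as the SD of FMA change. Response means a change above the acupuncture-arm median. The marker and FMA change are bivariate normal with correlation r = 0.3, 0.5 or 0.7 in each arm. The treatment effect is the same 6.59 points at every marker value, so by construction the marker says nothing about who benefits.

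**Step 1: AUC of a purely prognostic marker.** In the acupuncture arm, with a median split,

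AUC = 1/2 + (2/π) × arcsin(r/√2).

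At r = 0.5: 0.5 + 0.6366 × arcsin(0.3536) = 0.5 + 0.6366 × 0.3614 = 0.730. Neither δ nor σ appears in the formula, so the value is the same if acupuncture has no effect at all. Under sham the same cut-off lies 6.59/7.81 = 0.84 SD above the mean, giving about 20% responders. The sham and pooled values come from simulation.

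| Assumed r | Acupuncture | Sham | Pooled |
|---|---|---|---|
| 0.3 | 0.64 | 0.65 | 0.63 |
| 0.5 | 0.73 | 0.75 | 0.71–0.72 |
| 0.7 | 0.83 | 0.85 | 0.80–0.81 |

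In the same simulation the acupuncture-minus-sham difference is about 6.6 points in both high-marker and low-marker patients. The conclusion therefore does not depend on which arm or arms section 2.16 intends. The small gap between the arms' AUCs arises only because the cut-off falls at a different point of each distribution, so comparing AUCs by eye is no substitute for an interaction term.

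**Step 2: precision of the AUC.** With 17 responders and 18 non-responders in one arm, an AUC of 0.70 has a Hanley–McNeil 95% half-width of about 0.18.

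**Step 3 (secondary, conditional): optimism if features are picked and scored in the same patients.** Section 2.12.2.6 lists 16 referential leads. Section 2.12.2.8 says the study "will calculate coherence values between the seed region and all other regions" in two bands; section 2.12.2.7 gives four power bands. One possible count is 2 bands × 2 M1 seeds × 15 other leads = 60, less 2 for the C3–C4 pair counted twice, which is 58. Adding 4 × 16 = 64 powers gives 122. With pure noise, half responders, and between-feature correlation from 0.5 to 0, the mean best apparent AUC is:

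| Features screened | n = 35 | n = 70 |
|---|---|---|
| 4 | 0.64 | 0.60 |
| 8 | 0.66–0.68 | 0.61–0.62 |
| 58 | 0.72–0.75 | 0.66–0.68 |
| 122 | 0.74–0.77 | 0.67–0.69 |

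With 58 or 122 features, the uncorrected 95% CI of the best one excludes 0.5 in 76–100% of null trials. Section 2.12.2.8 says "the Bonferroni correction will be employed to control the false positive rate associated with multiple comparisons", but that sentence concerns the two-group coherence comparison. The model validation named in section 2.16 is goodness of fit of the logistic models.

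**Step 4: what the interaction test can deliver.** With the marker in SD units, the standard error of the arm × EEG slope is about √(2/n) residual SD, with n per arm. At n = 35 this is 0.239, so the 95% half-width is about 2.0 × 0.239 = 0.48. Simulated power for slopes of 0.25 and 0.50 is about 17% and 52% at 35 per arm, and 15% and 45% at 30 per arm.

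**The case against.** The ROC plan is a single sentence in a condensed article. It names no arm, and EEG is recorded in both. A reader might infer that the sham arm is ignored; the reference to acupuncture response leans that way, but the text does not say it. A reader might also infer that the AUC will be reported on the data used to choose the marker. That would follow if the only dataset described serves both purposes without validation, but the article does not state it. The feature list, responder rule and resampling may properly sit in a full protocol or SAP. These points stand, so the optimism concern is only conditional.

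The sentence can also be read as EEG change tracking clinical change, and the Introduction names prognosis as one intended use, which an AUC can serve. That stands too, but it does not rescue the wording about acupuncture response.

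The recovery figure covers 3–6 months, is not called spontaneous, and is said to vary with, among other things, how effective rehabilitation is; treatment here lasts two weeks. The figure should not be read as a forecast for this trial. The argument needs only that patients in both arms can improve for reasons other than acupuncture, and the rehabilitation given to all is enough for that.

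Finally, the EEG aim is exploratory and the interaction test is weak at this size. Both are true. Low power is a reason to label the result exploratory, not to let an AUC answer a question it does not address.

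**Conclusion.** The concern holds in this form: as written, the ROC analysis can support a prognostic statement about EEG but not a claim that EEG predicts response to acupuncture, because no marker-by-arm comparison is planned. This is a mismatch between the stated method and the stated question. Choosing an arm, cut-off or time point in an SAP would not remove it.

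The sizes are illustrative. The AUCs of about 0.64, 0.73 and 0.83 rest on assumed correlations of 0.3, 0.5 and 0.7 and a median split. The noise AUCs of 0.72–0.77 (n = 35) and 0.66–0.69 (n = 70) rest on 58 to 122 screened features and half responders, none of which the article fixes. The documents do not establish that the sham arm is left out or that selection and reporting share the same patients. The primary FMA comparison is not affected.

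**What to change.** Amend section 2.16 along these lines:

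- For baseline EEG features, base any statement about predicting acupuncture response on an ANCOVA of Day-15 FMA with baseline FMA, arm, EEG feature and arm × EEG, in all analysed patients from both arms. Report the interaction with its 95% CI, labelled exploratory.
- Report the AUC separately for each arm and call it prognostic.
- EEG change from baseline to Day 15 is measured after randomisation. Describe it only as associated with recovery.
- If features are screened and the AUC is reported in the same 70 patients, give an optimism-corrected AUC from resampling that repeats the selection step.

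The cost is analysis wording only: EEG and scales are already collected in both arms, and recruitment is planned until June 2028. The price is a weaker biomarker claim, with low power and wide intervals for the interaction. A null interaction should not be read as showing that EEG does not modify the effect.

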### Sample size calculation

2.7

Sample size for this study is estimated according to the formula for the comparison of means in a randomized controlled trial. Referring to the relevant literatures (26, 27), we estimate the pooled standard deviation (*σ*) of the treatment group and the control group to be 7.81, and the difference between the means of the two groups (*δ*) to be 6.59. We set the significant level (*α*) at 0.05, the Type II error rate (*β*) at 0.1, and the statistical power (1-β) at 0.9. After substituting the values into the formula, calculated sample size per group requires 30 cases. Considering a 15% dropout rate, a total of 70 cases will be enrolled.

$$n=\frac{2{\left(z_{\alpha }+z_{\beta }\right)}^{2}*\sigma^{2}}{\delta^{2}}$$

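### The only method named for EEG–outcome associations is an unadjusted Pearson or Spearman correlation with no provision for arm or baseline; if the arms are pooled, two separate treatment effects can look like a mechanism

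*Protocol article*

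**What the plan says.** Section 2.16 (Statistical analysis) of the protocol article names the method: "For correlation analysis, Pearson correlation will be applied to normally distributed continuous data, while Spearman correlation will be used for ordinal data". The type of data is the only selection rule. The sentence does not name the variables to be correlated, does not say whether the arms are combined, and gives no covariates.

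The purpose comes from elsewhere. The Introduction says that "EEG metrics will be linked with clinical outcomes, demonstrating its multiple values in efficacy assessment, mechanism interpretation, and prognosis prediction". The Discussion, referring to EEG changes before and after treatment, says "we aim to explore the neurophysiological mechanisms, by which acupuncture improve limb function in stroke patients, and screen EEG-based biomarkers with predictive value".

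The same section does spell out adjustment where it plans it. On continuous endpoints it says: "ANCOVA will be used to adjust for baseline values and confounders (e.g., age, gender, revascularization therapy status), with adjusted mean differences and 95% CIs reported". Logistic models with confounders are likewise described where the data are categorical. Neither is extended to the correlations. The Coherence analysis section (2.12.2.8) compares EEG between arms only, for example "non-parametric Wilcoxon test will be applied to compare Coherence differences between the two groups", and does not relate EEG to outcome. Section 2.16 also plans an ROC analysis of EEG as an indicator of response to acupuncture. No arm-adjusted EEG–outcome model or mediation model appears anywhere in the article.

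**The concern.** A two-variable correlation answers whether patients with larger EEG changes recover more only if nothing else moves both variables. In a randomised trial the obvious common cause is treatment. If acupuncture raises the mean motor score and also shifts the mean EEG measure, the two arms form two clouds displaced along a diagonal. The combined data then correlate even if, inside each cloud, EEG change says nothing about recovery. Reading that correlation as the route by which acupuncture works would only restate the two arm differences.

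Baseline is a second possible common cause. The Discussion says that recovery varies with lesion severity, and the inclusion criteria admit Brunnstrom stages II to IV from 1 week to 3 months after onset. If baseline severity is also related to EEG change, an unadjusted correlation absorbs that too, even within one arm.

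At stake is the mechanistic conclusion. The pooled correlation misleads when treatment affects both measures, which is when a mechanism is most likely to be claimed.

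**Working it through.** **Inputs from Sample size calculation (2.7).** On the spread, the article says "we estimate the pooled standard deviation (*σ*) of the treatment group and the control group to be 7.81". The planned effect is given as "the difference between the means of the two groups (*δ*) to be 6.59". On error rates and power it says: "We set the significant level (*α*) at 0.05, the Type II error rate (*β*) at 0.1, and the statistical power (1-β) at 0.9". Section 2.16 makes all tests two-sided at 5%. Section 2.7 does not name the outcome; I take it to be the primary motor score.

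**The plan's own figure.** n = 2(1.960 + 1.282)² × 7.81² / 6.59² = 29.5, so 30 per group, as stated. Adding 15% gives 30 × 1.15 = 34.5, so 35 per group and 70 in total, also as stated.

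**Planned motor effect in SD units.** d_F = 6.59/7.81 = 0.844.

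**EEG effect.** The documents give none, so d_E is assumed over 0 to 1.2 SD.

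**Expected pooled correlation.** With 1:1 allocation and zero correlation inside each arm, the between-arm covariance is d_E·d_F/4 and the pooled variances are 1 + d_E²/4 and 1 + d_F²/4. Hence

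r = (d_E·d_F/4) / √[(1 + d_E²/4)(1 + d_F²/4)].

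For d_E = 0.5: numerator 0.5 × 0.844/4 = 0.1055; denominator √(1.0625 × 1.178) = 1.119; r = 0.094. For d_E = 0.844: 0.178/1.178 = 0.151.

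**False-positive rate.** Simulation of 20,000 trials per scenario, with normal data, independent EEG and motor residuals within arm, and a two-sided 5% test:

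| Assumed EEG effect (SD) | Expected pooled r | Pooled Pearson, 30 per arm | Pooled Pearson, 35 per arm | Adjusted for arm, 30 per arm | Acupuncture arm alone, n = 30 |
|---|---|---|---|---|---|
| 0 | 0.00 | 5.0% | 4.8% | 4.8% | 5.0% |
| 0.3 | 0.06 | 7.2% | 7.6% | 5.0% | 5.0% |
| 0.5 | 0.09 | 11.1% | 12.3% | 5.0% | 4.8% |
| 0.844 | 0.15 | 21.3% | 24.0% | 4.9% | 4.9% |
| 1.2 | 0.20 | 34.4% | 39.0% | 5.1% | 5.2% |

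Pooled Spearman is within one percentage point of pooled Pearson throughout. With an EEG effect of 0.844 SD but no motor effect, the pooled rate is 5.1%, so inflation needs treatment effects on both variables.

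**Baseline, as illustration only.** If baseline severity correlates ρ with both changes and nothing else links them, the induced correlation is ρ². For assumed ρ of 0.3, 0.4 and 0.5 this is 0.09, 0.16 and 0.25. In a single arm of 30, simulated rejection rates are about 8%, 13% and 27%. The documents give no value for ρ.

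**The case against.** The strongest reply is that the article does not commit the error. A reader might infer from the bare correlation sentence that the arms will be pooled and treatment ignored. The text does not say so, and the sentence does not even mention EEG. The same tests run inside each arm would satisfy it and keep about 5%. The preceding sentence, on ROC analysis, looks at response to acupuncture, which makes a within-arm reading natural. Variable pairs and covariates for an exploratory analysis may also be settled in a fuller plan that is not shown.

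This stands as far as pooling is concerned, so the inflation above is conditional on it. It does not remove the point. The article fixes a two-variable method by name, writes out adjustment for its other analyses, and gives the EEG–outcome link a mechanistic role that an unadjusted correlation cannot carry. A within-arm split would cure the arm problem but leave baseline unadjusted.

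Three further limits are fair. Randomisation makes baseline EEG independent of arm, so pooling creates no spurious link between baseline EEG and outcome (the zero-effect row of the table). The documents connect severity with motor recovery but nowhere say that severity drives EEG change, so the baseline argument rests on an assumption. And the EEG work is exploratory.

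**Conclusion.** The concern holds in a conditional form. The article specifies only an unadjusted correlation and makes no provision for arm or baseline, although it intends EEG–outcome links to inform mechanism. If the arms are pooled and acupuncture affects both measures, a spurious mean r of about 0.06 to 0.20 and a false-positive rate of about 7% to 34% follow at 30 per arm. This assumes the planned 0.84 SD motor effect, EEG effects of 0.3 to 1.2 SD and no within-arm association. Adjusting for arm, or analysing the arms separately, returns the rate to about 5%.

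It would go too far to say that a false mechanism or biomarker finding is likely whenever the treatment works. The rates stay well below one half, the spurious correlations are modest, and an EEG effect is needed as well as a motor effect. Prognostic use of baseline EEG is not affected by pooling, and the primary FMA comparison is not affected at all. The change is worth making, but it is not critical to the trial.

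**What to change.** In section 2.16, for associations between EEG change and clinical outcome, replace the bare correlation with one of two adjusted analyses:

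- a partial correlation (Pearson or Spearman) adjusted for arm, baseline FMA and baseline EEG; or
- a regression of post-treatment FMA on EEG change with the same three covariates.

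Show the within-arm correlations alongside. State that a pooled unadjusted correlation will not be read as evidence of mechanism. Even the adjusted estimate remains an association, because EEG change is not itself randomised, and the text should say so.

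The cost is wording plus three degrees of freedom: with 60 completers, residual degrees of freedom fall from 60 − 2 = 58 to 60 − 5 = 55. Table 1 already schedules FMA and EEG before treatment and on Day 15, so no new data are needed. Ongoing recruitment is no obstacle if the change is made before the database is locked.
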